### Baseline and follow-up evaluation

The McLean Screening Instrument for Borderline Personality Disorder ((MSI-BPD) [32] and the SCID-5-PD will be conducted at baseline for diagnosis. Evaluation will take place at the completion of the 12-week and 16-week interventions and 16 weeks following the end of treatment to assess the change in BPD symptom using the MSI-BPD. All participants will be contacted for assessment at these time points regardless of treatment arm or continuation in treatment.

#### Symptom and psychosocial evaluation

Baseline measures administered at the assessment will include widely used valid and reliable measures of symptoms including BPD symptomatology, depression, disability and global functioning (see Table 1). These measures will be re-administered at the beginning and end of each block of treatment in both conditions. They will then be administered at 16-week follow-up interviews conducted following the end of treatment.

#### Service utilisation evaluation

Service utilisation data for 16 weeks prior to recruitment with this study and 16-week post-treatment follow-up will be collected for both groups regardless of the number of sessions attended. This will include presentations to the emergency department and inpatient settings, and length of engagement in these acute services.

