**Fig. 1 Fig1:**
[figure not shown]
Proposed trial design evaluating stepped group skills training interventions. Note. *All participants will be contacted 16 weeks post-intervention, independent of the number of sessions completed. **Number of participants expected at each time point (inclusive of a dropout rate of 30%)

The group skills treatment will involve two steps. The treatment group will be offered a weekly, 2-h group treatment for 12 weeks. Following completion of the 12-week group, suitability for inclusion in the second step of group treatment (16-week skills group) will be assessed based on group attendance and clinical indicators: criteria for inclusion in continuing treatment includes meeting > 4 BPD diagnostic criteria or severity on GAF (< 65) at the completion of the 12-week group. Similarly, participants in the TAU condition will be retained in treatment through the additional 16-week period based on clinical need.

DBT targets the development of skills in mindfulness, emotional regulation, distress tolerance and interpersonal effectiveness [17]. Two separate group treatment manuals will be developed for the treatment condition. The manualised treatments will be based on the DBT skills and provide structured therapeutic intervention. The 12-week manual will provide an introduction to target skills and an opportunity to practise within the group. Participants will be encouraged to practise skills between sessions and provide feedback in the following session. The 16-week manual will expand on skills introduced in the 12-week manual. It will be delivered in a similar format, including in-session and between-session practice with a review.

Treatment as usual (TAU) refers to typical care provided by the trial sites. Participants randomised to this condition will be referred to the care pathways typically used by the public mental health site. These referrals will be informed by clinical decision-making and the presenting issues of the participant. As such, a range of treatment settings may be accessed in the TAU condition including case management within the local community mental health service, mental health rehabilitation services, referral to a local private psychologist or psychiatrist with known experience in working with BPD, local non-government organisations, general practitioners (GPs) and family and carer services. The TAU referral pathway will be specifically tailored to the participant presentation.

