### Data management and linkage

Data will be managed according to the principles outlined in the NHMRC’s Australian Code for the Responsible Conduct of Research [24]. Specifically, the original data will be stored in hard copy and electronic form. Data will be entered into a database with no identifiable information other than a unique participant identification code. Electronic data will be encrypted and stored on a restricted access shared drive. De-identification of data will be managed by the 4th author. The research team will have access to the de-identified information on the shared drive for data analysis. Regular audits of data for data entry reliability and security will be conducted*.* A trial steering committee will be established with responsibility for overall research design, planning and implementation. Membership of the steering committee will include the chief investigator and representatives from all stakeholders, e.g. mental health service.

As part of this study, participants’ trial data will be linked with mental health service admission information from their electronic medical records.

Regular audits of the trial protocol will be provided to the funding body. This will include information regarding research design, implementation and participant recruitment and dropout. Alterations to the research protocol will be updated in the clinical trial registry (ANZCTR). Any adverse events will be reported to the Human Research Ethics Committee.

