### Primary outcomes

Two primary outcomes will be assessed in this study: symptom reduction and service utilisation. Specifically, the reduction in BPD symptom severity and associated mental health symptoms will be measured by the MSI-BPD total score [32], and the use of health services including emergency department visits and inpatient admissions will be assessed to evaluate the efficacy of the two treatment conditions.

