#### Economic analyses

An important component of this study will be to examine and compare the cost-effectiveness and efficacy of the stepped individual and skills group interventions. Using a pragmatic clinical trial design, this study will include the routine costs and healthcare service utilisation costs associated with the implementation of both interventions. Service utilisation data, e.g. the number of presentations and admissions will be used to compare healthcare service costs between the two treatment groups. Although healthcare costs are measured in monetary terms, clinical effectiveness is determined independently in terms of clinical outcomes. A cost-effectiveness analysis will be performed [7].

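### The planned service-use windows leave out weeks 0–36, which the mixed model and the cost analysis both need, and the anchor of the post-treatment window is unclear

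*Protocol article*

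**What the plan says.** All references are to the protocol article.

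- **Primary outcomes:** "Two primary outcomes will be assessed in this study: symptom reduction and service utilisation".
- **Service utilisation evaluation:** "Service utilisation data for 16 weeks prior to recruitment with this study and 16-week post-treatment follow-up will be collected for both groups". This holds whatever the number of sessions attended. It covers emergency and inpatient presentations and the length of those contacts.
- **Primary analyses:** the same linear mixed model is applied to MSI-BPD and to service use. Change from baseline to the end of the 16-week block is of main interest. Three time points are used, so that change during treatment and its maintenance afterwards can also be examined.
- **Economic analyses:** "this study will include the routine costs and healthcare service utilisation costs associated with the implementation of both interventions". Numbers of presentations and admissions feed the cost comparison.
- **Data management and linkage:** "trial data will be linked with mental health service admission information from their electronic medical records". No period is given.
- **Timing of follow-up:** the Fig. 1 note says "All participants will be contacted 16 weeks post-intervention, independent of the number of sessions completed". Baseline and follow-up evaluation places the last assessment 16 weeks after treatment ends and adds: "All participants will be contacted for assessment at these time points regardless of treatment arm or continuation in treatment". Table 1 shows the 12-week group in weeks 4–16, the 16-week group in weeks 20–36, treatment as usual (TAU) in weeks 4–36, and a single follow-up column at week 52.
- **When treatment ends (Study design):** entry to the second group step depends on attendance and on diagnostic criteria or GAF after the first step. In the other arm, "participants in the TAU condition will be retained in treatment through the additional 16-week period based on clinical need".

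**The concern.** The data section, the analysis section and the economic section describe service use over different periods. If collection follows the data section, acute care between randomisation and the end of treatment does not enter a primary outcome. A difference between arms that arises while treatment is being delivered, in either direction, would then be missing from the primary comparison and from the cost comparison.

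The second issue is where the post-treatment window starts. If it starts when each person's treatment ends, its position depends on events after randomisation, and those events follow different rules in the two arms. The arms could then be compared over different stretches of time since randomisation.

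**Working it through.** **The plan's own figure.** The only sample-size figure concerns MSI-BPD. The difference is 0.16 × 8.16 = 1.3056 with SD 2.08. With two-sided alpha 0.05 (sidedness is assumed) and 80% power, n = 2 × (1.960 + 0.842)² × 2.08² / 1.3056² = 39.8, so 40 per group. Then 40 / 0.70 = 57.1, so 58 per group. Both reproduce the article. Neither bears on service use, for which the article gives no event rate and no power statement.

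**Inputs, from Table 1.** Recruitment, baseline and randomisation are at week 0. Treatment spans weeks 4–36. Follow-up is at week 52. The post-treatment window lasts 16 weeks.

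**Coverage if the window is weeks 36–52 for everyone:**
- counted: 52 − 36 = 16 weeks; 16/52 = 30.8%
- not counted: weeks 0–36; 36/52 = 69.2%
- of these, the scheduled treatment period: 36 − 4 = 32 weeks; 32/52 = 61.5%

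**Coverage if the window follows each person's own end of treatment:**
- step 1 only, ending at week 16: 16 + 16 = 32, so weeks 16–32
- step 2, ending at week 36: 36 + 16 = 52, so weeks 36–52
- overlap: max(0, 32 − 36) = 0 weeks
- not counted for the step-1-only participant: weeks 0–16 and 32–52, i.e. 16 + 20 = 36 weeks, again 69.2%

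The uncounted share of the 52 weeks is therefore the same on both readings, and each person's treatment weeks lie outside the window on both.

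**Data against analysis.** The two windows give two service-use values per person, one before recruitment and one after treatment. The mixed model calls for three time points. Its main contrast needs a value that reflects service use up to the end of the 16-week block (week 36), and neither window supplies one.

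**Data against costs.** Costs of acute care incurred while the interventions are delivered fall in weeks 4–36. The planned windows exclude those weeks.

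**Anchor.** The Fig. 1 note, Baseline and follow-up evaluation and Service utilisation evaluation all refer to the end of the intervention or treatment. Table 1 refers to week 52. The two agree only for a participant whose treatment ends at week 36.

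**The case against.** Hypothesis 3 concerns admissions and acute care following treatment. Equal 16-week windows before recruitment and after treatment answer that question, so the windows are not an error for that hypothesis. This stands. Making weeks 0–52 the primary estimand would be a different choice, and a debatable one with 125 participants already recruited to a non-blind trial.

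A reader might infer that acute care during treatment will never be captured. The article does not support that. The record linkage has no stated period, and the analysis and economic sections suggest that treatment-phase data may be wanted. What can be said is that the only section that sets collection periods does not plan for those weeks. The linkage sentence names admission information only, so emergency presentations cannot be assumed to be covered.

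A reader might also take the window as settled at each person's own end of treatment, with TAU having no end at all. That goes too far. Table 1 gives TAU weeks 4–36 and one follow-up at week 52, and everyone is to be contacted regardless of continuation. A common window at weeks 36–52 is a natural reading. The anchor is ambiguous.

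Nor do the documents show that differing windows bias the comparison in a known direction, or how much precision longer counting would gain. Either claim would need service-use rates over time, and the article gives none.

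Lastly, the article condenses a fuller protocol that is not shown. That would excuse missing detail. It does not remove a conflict between periods and analyses that the article itself states.

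**Conclusion.** The concern holds as a conflict between sections. As written, the collection plan omits weeks 0–36, which is 36 of 52 post-baseline weeks (69%) and includes all scheduled treatment weeks 4–36. Followed as written, it cannot supply the three-time-point model for service use or the service-use costs of delivering both interventions. The start of the post-treatment window is also unclear. The literal wording allows windows with no overlap between step-1-only and step-2 participants, while Table 1 points to one common window.

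The percentages rest only on the weeks in Table 1 and a 16-week window. The size of any bias or loss of power cannot be given from the document. The point deserves correction because service use is a primary outcome and the remedy is modest. It does not invalidate the post-treatment comparison that Hypothesis 3 asks for.

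**What to change.** 1. Extract emergency presentations, admissions and bed-days from randomisation to week 52 for every randomised participant in both arms. Confirm that the record linkage covers emergency presentations, and add them if it does not.
2. Use the full period for the cost-effectiveness analysis and for the during-treatment time points of the mixed model.
3. Keep the post-treatment comparison for Hypothesis 3, but fix it at weeks 36–52 from randomisation in both arms, with the 16 weeks before recruitment as baseline.
4. Bring Baseline and follow-up evaluation, Service utilisation evaluation, Primary analyses, Economic analyses and Table 1 into line with each other.

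The cost is a longer record extraction and a registry and ethics amendment. No extra visits are needed for the service-use data. Because the trial is non-blind and recruitment is under way, the amendment should be dated and lodged before any comparison by arm.

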### Data management and linkage

Data will be managed according to the principles outlined in the NHMRC’s Australian Code for the Responsible Conduct of Research [24]. Specifically, the original data will be stored in hard copy and electronic form. Data will be entered into a database with no identifiable information other than a unique participant identification code. Electronic data will be encrypted and stored on a restricted access shared drive. De-identification of data will be managed by the 4th author. The research team will have access to the de-identified information on the shared drive for data analysis. Regular audits of data for data entry reliability and security will be conducted*.* A trial steering committee will be established with responsibility for overall research design, planning and implementation. Membership of the steering committee will include the chief investigator and representatives from all stakeholders, e.g. mental health service.

As part of this study, participants’ trial data will be linked with mental health service admission information from their electronic medical records.

Regular audits of the trial protocol will be provided to the funding body. This will include information regarding research design, implementation and participant recruitment and dropout. Alterations to the research protocol will be updated in the clinical trial registry (ANZCTR). Any adverse events will be reported to the Human Research Ethics Committee.

### Primary outcomes

Two primary outcomes will be assessed in this study: symptom reduction and service utilisation. Specifically, the reduction in BPD symptom severity and associated mental health symptoms will be measured by the MSI-BPD total score [32], and the use of health services including emergency department visits and inpatient admissions will be assessed to evaluate the efficacy of the two treatment conditions.

### Data analysis plan

#### Characteristics of the sample

Descriptive statistics will be used to summarise the clinical and demographic characteristics of the sample at baseline.

#### Primary analyses

The effect of treatment on primary outcomes will be evaluated using a linear mixed models approach, to account for the repeated measured structure of the data (SPSS-25). The data will be analysed as an intention-to-treat with time as a repeated measure. Recommended as the gold standard for study designs of this nature, this design (i) allows for the assessment of individual trends over time, with sensitivity to detect change; (ii) takes into account the longitudinal nature, utilising all data available; and (iii) controls for any pre-intervention differences [9, 27]. A linear mixed models analysis will be performed for each primary outcome variable symptom reduction (total number of BPD symptoms measured by the MSI-BPD) and service utilisation (inpatient hospital admissions and emergency department presentations). Change over time on these variables will be modelled as a within-subject effect of time, and the effectiveness of the intervention conditions will be determined by significant two-way group × time interaction. Although the change between baseline and end of the 16-week treatment block is of primary interest, three time points will be included to also examine the change during treatment and whether any changes are maintained following treatment. Within- and between-group effect sizes will be calculated, compared and interpreted according to the Cohen [5] recommendations.

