### Sample size and power analysis

A clinically meaningful difference was defined as a reduction of 16% or more in the number of BPD symptoms, according to the MSI-BPD. This estimate is informed by previous studies using this measure, clinical judgement and existing trials examining shortened skills-based interventions for BPD [21, 22]. For this trial, the difference to be detected was calculated using the mean baseline MSI-BPD score (8.16) and standard deviation (2.08) in Miller et al. [22]. The reduction of 16% represents the within-subject mean symptom reduction at the end of the 16-week treatment block, relative to the individual’s baseline. Thus, based on a power of 80%, an alpha level of .05, the total number of participants required in each group is 40. However, accounting for a drop-out rate of 30%, 58 participants will need to be recruited for each group (N = 116).

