### Participant randomisation

Following diagnostic assessment, participants will be randomly allocated to one of the treatment arms using a computerised randomisation programme, QMinim. QMinim uses a minimization method to generate an imbalance score for each participant based on prognostic factors. Allocation is then made to ensure minimum imbalance between the groups. Randomness is incorporated into the generated algorithm to maintain blindness [28]. Blocking is used to ensure equal numbers within each condition. Participants will be allocated to each treatment arm on a 1:1 ratio. Minimization prognostic factors are age, gender, GAF score severity, self-harm ideation and suicide attempts to control for these variables and allow for balanced groups. Treatment allocation will be concealed from the researchers administering assessments to prospective participants to ensure bias cannot be introduced into the allocation process.

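### The DBT arm is treated in therapy groups and TAU is not, but the primary model and the sample size make no allowance for clustering within those groups

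*Protocol article*

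**What the plan says.** Randomisation is individual: "Participants will be allocated to each treatment arm on a 1:1 ratio" (Participant randomisation). Under Study design, both steps of the experimental arm are delivered in groups. For the first step, "The treatment group will be offered a weekly, 2-h group treatment for 12 weeks"; those who meet the continuation criteria are then considered for a 16-week skills group. Members practise skills in session and report back at the next one. TAU is a referral fitted to each patient, and no shared therapy group is specified for it.

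Under Primary analyses, treatment effects are evaluated "using a linear mixed models approach, to account for the repeated measured structure of the data". Effectiveness is judged by the interaction of group with time, where group means trial arm. The change of main interest runs from baseline to the end of the 16-week block. The same model serves both primary outcomes, MSI-BPD and service use. No therapy-group term is named.

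Under Sample size and power analysis, the target is defined as follows: "A clinically meaningful difference was defined as a reduction of 16% or more in the number of BPD symptoms, according to the MSI-BPD". The result is: "based on a power of 80%, an alpha level of .05, the total number of participants required in each group is 40". After 30% dropout this becomes 58 per arm, 116 in total. No group size, ICC or design effect is given.

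**The concern.** Patients in the same skills group share sessions, peers and group process, so their outcomes may be correlated. TAU patients have no such shared unit in the plan. If the DBT-arm outcomes are positively correlated within therapy groups, the variance of that arm's mean change is larger than a model with independent patients reports. P-values are then too small and confidence intervals too narrow. Intervals that are too narrow would flatter either kind of claim the article mentions: the superiority design under Study design or the equivalent reductions hypothesised under Objectives. The stated 80% power would also exceed what an analysis with valid error control can deliver.

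**Working it through.** **Inputs from the protocol article (Sample size and power analysis):** baseline MSI-BPD mean 8.16, SD 2.08, reduction 16%, alpha 0.05, power 80%, dropout 30%. Sidedness is not stated; the two-sided calculation reproduces the stated figure (one-sided gives 32).

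**Step 1: reproduce the plan's figure.**
- Difference: 0.16 × 8.16 = 1.3056 points; standardised, 1.3056 / 2.08 = 0.628.
- n per arm = 2 × (1.96 + 0.842)² / 0.628² = 39.8, so 40. Power at 40 per arm is 0.802.
- Recruited: 40 / 0.70 = 57.1, so 58 per arm, 116 in total.

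Both stated figures are those for independent patients, so they contain no hidden allowance for clustering.

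**Step 2: put clustering in the DBT arm only.** Let m be the number of evaluable patients per therapy group. Neither m nor the ICC is in the document; both are assumptions. With equal arms, the ratio of true to naive variance of the difference is

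R = {[1 + (m − 1) × ICC] + 1} / 2.

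Under the normal approximation, with z = 0.628 / √(2/40) = 2.81:
- type I error of the test that ignores clustering = 2 × [1 − Φ(1.96 / √R)];
- power of the test that ignores clustering = Φ((z − 1.96) / √R);
- power of a test that models clustering = Φ(z / √R − 1.96).

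| m | ICC | R | SE ratio √R | Type I error, clustering ignored | Power, clustering ignored | Power, clustering modelled |
|---|---|---|---|---|---|---|
| 8 | 0.01 | 1.035 | 1.017 | 5.4% | 80% | 79% |
| 6 | 0.02 | 1.050 | 1.025 | 5.6% | 80% | 78% |
| 8 | 0.05 | 1.175 | 1.084 | 7.1% | 78% | 74% |
| 10 | 0.10 | 1.450 | 1.204 | 10.4% | 76% | 64% |
| 12 | 0.10 | 1.550 | 1.245 | 11.5% | 75% | 62% |

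The type I error and the last column belong to different tests. The first is the cost of leaving clustering out; the second is the power left once it is put in.

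**Step 3: numbers needed for 80% power with clustering modelled.** n per arm = (39.84 / 2) × (2 + (m − 1) × ICC).
- m = 8, ICC 0.05: 19.92 × 2.35 = 46.8, so 47 evaluable and 47 / 0.70 = 67.1, so 68 recruited per arm (136 in total).
- m = 6, ICC 0.02: 19.92 × 2.10 = 41.8, so 42 evaluable and 60 recruited per arm (120).
- m = 12, ICC 0.10: 19.92 × 3.10 = 61.8, so 62 evaluable and 89 recruited per arm (178).

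**Step 4: allow for actual recruitment.** Trial status reports 125 recruited. Assuming an equal split and 30% dropout, 62.5 × 0.70 = 43.75 per arm are evaluable. Power is then 84% without clustering. With clustering modelled and m = 8, it is 81% at ICC 0.02 and 77% at ICC 0.05. The type I error column does not change, because R does not depend on n.

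**Step 5: few clusters.** Forty evaluable patients in groups of 8 make 40 / 8 = 5 therapy groups. Small-sample degrees of freedom would bring the modelled power somewhat below the normal-approximation figures.

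**The case against.** The strongest reply is that the size of the problem cannot be read from the document. Group size and ICC are assumed, and at ICC 0.01 with 8 per group the loss is about one point of power. If 8 is the enrolled size and 30% drop out, about 8 × 0.70 = 5.6 remain, and at ICC 0.05 the type I error is 6.3%, not 7.1%. This stands: the direction is firm for any positive ICC, the magnitude is not.

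A second reply is that the stated 80% belongs to a two-sample comparison with a baseline SD, not to the repeated-measures model. The power of that model depends on a baseline-to-follow-up correlation that is not given, and it could be higher or lower. This also stands. The figures isolate the effect of clustering; they do not predict the power of the final analysis.

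A third is that the stated purpose of the mixed model is not a complete list of random effects, and an analysis plan not shown could add a therapy-group term. It could. But the article does state which dependence the model handles, and it fixes the sample size at the independent-patient figure. The point rests on those two statements, not on silence.

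A reader might infer that a single test suffers both the 7.1% error and the fall in power to 74%. It does not: the test that ignores clustering keeps about 78% power in that case. A reader might also infer that every DBT patient shares therapists and peers. The article says that groups are offered, and it does not describe therapist allocation or whether groups are closed or rolling.

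**Conclusion.** The concern holds as a mismatch between a group-delivered arm and an analysis and sample size built on independent patients. For any positive within-group ICC, the standard error of the arm × time contrast is understated and 80% is too high a power for a valid analysis. With 6 to 12 evaluable patients per group and ICC 0.02 to 0.10, both assumed, the type I error is about 5.6% to 11.5% if clustering is ignored. Power at 40 per arm is about 78% to 62% if it is modelled, and somewhat lower with few groups. Recruitment above plan makes up the power loss at low ICC but only partly at m = 8 and ICC 0.05, and it does nothing for the type I error. The documents do not support saying that the distortion is known to be large. It is slight at ICC 0.01 and becomes material from about 0.05. The change should be made before analysis.

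**What to change.** - Record the therapy-group identifier for each DBT patient, for both steps. Attendance already informs suitability for the second step, so membership should be available.
- Add a random therapy-group effect in the DBT arm only that acts on post-baseline change: either therapy group × time, or a therapy-group effect on post-baseline values with baseline as covariate. A time-constant random coefficient on the arm indicator will not do. It is the same at baseline and follow-up, cancels from each patient's change, and leaves the standard error of the arm × time contrast uncorrected.
- Use Satterthwaite or Kenward-Roger degrees of freedom.
- State in advance how membership is defined for patients who move to the 16-week group and for those who never attend, since the main contrast ends after the second step.
- Report the estimated ICC.
- Restate the power behind "the total number of participants required in each group is 40" over a range of ICC and group size.

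The cost is one data field, one model term and a short rule on membership; treatment, visits and recruitment need not change. The price is wider confidence intervals, a lower stated power, and a variance component estimated imprecisely from few groups.

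### Service utilisation is collected in two windows only, so the planned three-time-point interaction model does not fit it, and leaving the pre-recruitment count out as a covariate costs about half the power or more

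*Protocol article*

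**What the plan says.** The protocol article's section on primary outcomes states: "Two primary outcomes will be assessed in this study: symptom reduction and service utilisation". The section on primary analyses then fixes one method for both: "A linear mixed models analysis will be performed for each primary outcome variable". For the second outcome it names the variables as "service utilisation (inpatient hospital admissions and emergency department presentations". The criterion is that "the effectiveness of the intervention conditions will be determined by significant two-way group × time interaction". The same paragraph gives the change from baseline to the end of the 16-week treatment block as the main interest and adds that "three time points will be included to also examine the change during treatment". No link function, transformation or count model is named.

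The section on service utilisation evaluation describes a different data structure: "Service utilisation data for 16 weeks prior to recruitment with this study and 16-week post-treatment follow-up will be collected for both groups". The content is "presentations to the emergency department and inpatient settings, and length of engagement in these acute services". In Table 1 treatment runs from week 4 to week 36. Utilisation in that period is not described as collected.

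The sample size section rests on the MSI-BPD alone. No event rate, dispersion, share of zeros, target effect or power is given for utilisation.

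**The concern.** There are two separate difficulties.

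First, the model and the data do not match. An outcome observed once before recruitment and once after treatment has no value at the end of the 16-week block. It supports neither three time points nor the contrast that the plan calls primary.

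Second, what remains of the plan with two windows is an inefficient test. A group × time interaction on two occasions compares raw change between arms, so all the noise in the pre-recruitment count enters the outcome at full weight. That count may be both noisy and high, because referral comes through the intake line or the emergency department, for self-harm and suicidal ideation among other reasons. An additive Gaussian model can also imply negative counts and can be dominated by a few frequent attenders.

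At stake is a primary outcome with no stated power. Hypothesis 3 expects an equivalent reduction in admission length and acute care, so a non-significant interaction from a weak test could be misread as support for it.

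**Working it through.** **The plan's own figure (MSI-BPD only).** Difference = 0.16 × 8.16 = 1.3056; SD 2.08; two-sided alpha 0.05 (sidedness is not stated, but two-sided reproduces the result); power 80%. n per arm = 2 × (1.96 + 0.84)² × (2.08 / 1.3056)² ≈ 39.8, so 40. With 30% dropout, 40 / 0.70 = 57.1, so 58. Both figures reproduce. Neither says anything about utilisation.

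**What the interaction becomes.** With two occasions, complete data and unconstrained baseline means, the group × time estimate is (mean post − mean pre) in one arm minus the same in the other. Its variance per participant is Var(pre) + Var(post) − 2Cov. With the pre count as covariate and pooled slope b, it is Var(post) − 2b·Cov + b²·Var(pre).

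**Hand calculation (all rates assumed).** Take a treatment-as-usual (TAU) post mean of 1 and a rate ratio of 0.5, so the effect is 0.5 events. Variance = mean + 2 × mean² (negative binomial k = 0.5), and half the between-person variation is shared between windows, so Cov = 0.5 × 2 × (pre mean) × (post mean). Then Var(post) = 3 in TAU and 1 in the group arm.

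*Equal windows (pre mean 1).* Var(pre) = 3; Cov = 1 and 0.5.
- Change: 3 + 3 − 2 = 4 and 3 + 1 − 1 = 3; sum 7. At 40 per arm SE = √(7/40) = 0.418, z = 1.20, power 22%. At 58 per arm, 30%.
- Adjusted: b = 0.75/3 = 0.25; 3 − 0.5 + 0.1875 = 2.6875 and 1 − 0.25 + 0.1875 = 0.9375; sum 3.625. At 40 per arm SE = 0.301, z = 1.66, power 38%. At 58 per arm, 52%.

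*Inflated pre-window (pre mean 2).* Var(pre) = 2 + 2 × 4 = 10; Cov = 2 and 1.
- Change: 10 + 3 − 4 = 9 and 10 + 1 − 2 = 9; sum 18. At 40 per arm SE = 0.671, z = 0.75, power 12%. At 58 per arm, 15%.
- Adjusted: b = 1.5/10 = 0.15; 3 − 0.6 + 0.225 = 2.625 and 1 − 0.3 + 0.225 = 0.925; sum 3.55. Power 39% at 40 per arm and 52% at 58.

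Both methods here are Gaussian, so this gap owes nothing to the error distribution.

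**Simulation, equal windows.** 600 trials per scenario, rate ratio 0.5, variance = mean + alpha × mean², so k = 1/alpha. Entries are power.

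| n/arm | mean, alpha, shared | Change | Gaussian ANCOVA | Negative binomial, adjusted |
|---|---|---|---|---|
| 40 | 0.5, 2, 0.5 | 0.168 | 0.267 | 0.298 |
| 40 | 1, 2, 0.5 | 0.228 | 0.368 | 0.445 |
| 40 | 1, 4, 0.5 | 0.180 | 0.267 | 0.377 |
| 40 | 2, 2, 0.5 | 0.267 | 0.483 | 0.503 |
| 58 | 1, 2, 0.5 | 0.327 | 0.503 | 0.548 |
| 58 | 2, 2, 0.5 | 0.413 | 0.632 | 0.652 |
| 58 | 1, 1, 0.5 | 0.335 | 0.658 | 0.693 |

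Over all 12 scenarios run, the change test had 17–41% power against 30–69% for negative binomial, a relative loss of 37–52%. Negative binomial exceeded Gaussian ANCOVA by 2 to 8 points in 11 scenarios and by 11 in the other (40 per arm, alpha 4), where its null rejection rate was 8.3%.

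**Size.** Under the null the change test rejected in 4–6% of trials and negative binomial in 5–10%. Three scenarios were rerun at rate ratio 0.5 with size-adjusted critical values. Gaussian ANCOVA and negative binomial then had almost the same power: 0.366 and 0.372, 0.382 and 0.380, 0.560 and 0.560. The change test had 0.194, 0.205 and 0.335.

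**Simulation, inflated pre-window.** 400 trials per scenario, pre to post means 1.5 to 0.8 and 2.0 to 1.0, rate ratio 0.5. At 40 per arm the change test had 9–15% power against 38–52% for negative binomial; at 58 per arm, 14–23% against 52–65%. Gaussian ANCOVA reached 34–48% at 40 per arm.

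**The case against.** The strongest defence is that the text does not force a raw-change test. It says that the design controls for pre-intervention differences, and a mixed model constrained to a common baseline mean behaves like ANCOVA. The parameterisation could sit in an analysis plan that is not shown. This stands as a condition: the efficiency loss applies only if baseline means are left free. It does not remove the mismatch between two windows and three time points. Records linked for admissions might supply events during treatment, but the article does not say that they will be used.

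It is also fair to say that utilisation is to be collected regardless of sessions attended, so 40 per arm may be too pessimistic. Results at 58 per arm are therefore shown, and the loss persists there.

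A reader might infer that the Gaussian model itself throws away most of the power. The comparison does not support that: Gaussian ANCOVA recovers most of the gap in nearly every scenario, and virtually all of it after size adjustment where that was checked. Powers near 10% likewise hold only if the pre-recruitment mean is well above the post-treatment mean. Inflation is plausible from the referral routes, but no figure in the document establishes it, nor that the counts are sparse. Nor is there a false-positive problem, since the planned test holds its level.

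**Conclusion.** The point holds in a limited form. The article fixes a model for service utilisation that its own data collection cannot feed: two windows against three time points, with no value at the end of the 16-week block. If the model is reduced to two windows with unconstrained baseline means, it is valid but inefficient. For a rate ratio of 0.5 and 40 to 58 per arm, its power is roughly half that of a baseline-adjusted analysis when the windows have equal means, and about a quarter to a third when the pre-recruitment window is inflated. The main cause is that the pre-recruitment count is not used as a covariate. The choice of Gaussian error is secondary.

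The size of the loss rests on assumed event rates (means 0.5 to 2 per window, k 0.25 to 1), because the document gives none. The structural mismatch rests on the text alone. Confidence is moderate.

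**What to change.** For ED presentations and admissions, replace the group × time linear mixed model with a model of the post-treatment count that adjusts for the pre-recruitment count. This gives the main gain. Preferably use negative binomial regression with log observation time as offset, and report a rate ratio with 95% CI. Check its type I error by simulation at the achieved sample size, or use robust or bootstrap inference, because it can be mildly anti-conservative here. Keep an additive mean difference with a bootstrap CI for the cost analysis. Limit the three-time-point mixed model to the MSI-BPD, and reword the primary analyses section so that it agrees with the two utilisation windows.

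The cost is analysis wording and a little programming, with no new data or participants. The downside is that the effect is on a ratio scale, which the additive difference partly offsets.
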